#### Clinical assessment

During the study visits, participants will undergo the following data collection procedures
i.Study questionnaire will be administered to all participants. The questionnaire booklet will be self-completed by the participant.ii.A 1 min cognition test will be performed where the participant names as many animals as possible from memory [48].iii.DAS28: Tender and Swollen joint count assessment: 28 joints, the 10 metacarpophalangeal (MCP), 10 proximal interphalangeal (PIP), 2 wrist, 2 elbow, 2 shoulder and 2 knee joints will be examined for tenderness and swelling [49]. Patient Global Assessment (PGA) of disease activity will be assessed using a visual analogue scale. DAS28-ESR will be estimated using the following formula

Equation 1: DAS28 ESR Calculation [50]
$$ DAS28=0.56\times \sqrt{TJC}+0.28\times \sqrt{SJC}+0.70\times \ln ESR+0.014\times PGA $$iv.Quantitative sensory testing will be conducted using Pressure Pain detection Threshold (PPT), Temporal Summation (TS) and Conditioned Pain Modulation (CPM) tests. PPT involves the assessment of mechanical pressure pain thresholds using a handheld computerised pressure algometer (Medoc Algomed – Computerised Pressure Algometer). The algometer consists of a rod with a 1 cm diameter circular end and is applied perpendicular to the test site. Pressure is applied through the algometer at a standardised rate until the participant presses a button indicating a change in sensation from pressure to pain, when the algometer is immediately removed and the pressure reading recorded. Three measurements will be collected at each site, with a short rest between measurements. Participants will be familiarized with the procedure by performing it on a different test site before commencing the test. PPT will be conducted on three anatomical sites, the body of the brachioradialis muscle of the non-dominant forearm, the medial tibiofemoral joint line, and the body of the tibialis anterior muscle of the dominant side [51].Temporal summation (TS) tests the nervous systems responsiveness to repeated noxious stimuli. It will be conducted using a supra-threshold pinprick stimulator (256mN pinprick), which is applied repeatedly to a single point on the skin over the patella ligament, in a single test and on a train of 10 repetitions, with intervals of 1 s in between repetitions. The participants will be asked to indicate the intensity of pain on a 0–100 visual analogue scale (where 0 represents no pain and 100, the most intense pain imaginable) for the single test, and the average pain intensity for the series. The difference between the 2 self-reports will be used to measure TS.Conditioned Pain Modulation (CPM) is conducted using the PPT test (test stimulus). The test stimulus is applied to the body of the tibialis anterior muscle contralateral to the participant’s dominant hand before and after induction of a painful stimulus at a remote anatomical site. This conditioning stimulus is achieved by applying a blood pressure cuff to the dominant arm and inflating until the radial pulse can no longer be palpated. The participant may be asked to perform hand exercises (squeezing a stress ball) to induce exercise induced ischaemic pain or discomfort. As soon as the pain or discomfort in the forearm is rated as 4/10 by the participant, they stop squeezing the ball and the second PPT test is performed. Only one CPM test will be performed. CPM is calculated as [52]:

Equation 2: CPM Calculation
$$ CPM= PPTpost- PPTpre $$xxii.Joint inflammation (synovitis and tenosynovitis) will be assessed by ultrasound scans of the hands and feet in both grayscale (GS) and power Doppler (PD) modes. Examinations will be conducted according to the EULAR guidelines for MSK ultrasound scans in rheumatology [53]. Joint inflammation will be assessed using the OMERACT US group scoring criteria [54, 55].xxiii.Blood samples will be obtained for inflammatory biomarker (Erythrocyte Sedimentation Rate (ESR), and C-Reactive Protein (CRP) assays, and samples may be stored for additional biomarker analyses.

#### Additional data collection

The CAP-RA questionnaire will, in addition, be mailed for completion by 80 consecutive participants 1 week after the baseline visit, to assess test-retest reliability.

The course of fatigue and pain will be assessed by sending participants weekly SMS text messages at approximately the same time each week, with the question “On a scale of 0 – 10, with 0 indicating no pain, and 10 indicating the worst imaginable pain, how would you rate your pain during the past week? Please respond to this message with a number. Thank you”. The equivalent question wording will be used to ask about weekly fatigue.

### Statistical analysis

The primary objective of the study is to determine the psychometric properties of the new CAP-RA questionnaire. The psychometric properties examined will include structural validity, construct hypothesis testing, internal consistency, reliability, measurement error and criterion validity, in accordance with Consensus-based Standards for the selection of health Measurement Instruments (COSMIN) guidelines [56–58].

Structural validity measures the degree to which the scores in a patient reported outcome measure reflect the dimensionality of the construct to be measured. Structural validity will be assessed using confirmatory factor analysis (CFA) and Rasch modelling. A suitable polytomous Rasch model will be selected [56]. The unidimensional and local independence assumptions will be examined and model fit parameters will be estimated [59]. The construct validity of the CAP-RA questionnaire, a measure of the degree to which scores are consistent with a hypothesis that is based on the assumption that the PROM validly measures the intended construct, will be investigated using confirmatory factor analysis. Appropriate fit statistics will be calculated [60]. Internal consistency, which is a measure of the degree of interrelatedness among items in the questionnaire will be estimated using Cronbach’s alpha, with a value greater than 0.70 signifying acceptable internal consistency [61].

Test-retest reliability will be estimated using the Intraclass Correlation Coefficient, with acceptable values ≥0.70 [62]. Measurement error will be estimated by the Standard Error of Measurement (SEM), Smallest Detectable Change (SDC) and the Limits of Agreement (LoA). Criterion validity will be a measure of the degree to which the instrument is an adequate reflection of central sensitisation.

The relationship between baseline CAP-RA scores and pain outcomes will be measured using regression analysis, with 12-week pain as the outcome variable and baseline characteristics as covariates.

Secondary objectives will be addressed using appropriate regression analysis. For example, the association between fatigue and central sensitization will be examined using linear or non-linear regression analysis, based on the distribution of the data, and the course of fatigue will be examined using linear or non-linear mixed effect models as indicated. CAP-RA questionnaire thresholds for delimiting high levels of central pain mechanisms will be derived through receiver operating curves plotted using dichotomised outcome measures, such as the different QST measurements [56, 63].

Analyses will be undertaken using appropriate statistical software. *P* values less than or equal to 0.05 will be considered statistically significant unless otherwise stated.

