### Limitations

Although a brief questionnaire may be acceptable to patients, and feasible in busy clinical practice or large epidemiological studies, its interpretation is inevitably limited by its self-reported nature, and even validated self-report instruments are prone to recall bias. Traits assessed with the CAP-RA questionnaire are however multifaceted and subjective precluding objective measurement. We attempt to address this by testing CAP-RA against QST, as a proxy for central pain mechanisms. However, there is no gold standard for measuring CS which is itself a multidimensional construct. We will use a brief QST procedure which has been used in other research studies to measure central pain mechanisms, comprising both static (PPT) and dynamic (TS and CPM) test modalities. Each QST modality might have different measurement properties and indicate different aspects of CS including spinal processing of nociceptive signals and descending modulation. Only two timepoints will be measured, and this study was not designed to measure the ability of CAP-RA to predict persistent pain in RA beyond 3 months. This study will be conducted within a restricted geographical region (within the East Midlands of the UK) with people who have active rheumatoid arthritis measured by DAS28. Our findings might have limited generalizability outside this population. More bias may also occur with the weekly SMS text messages, as subgroup of participants opting in to this section of the study may not be representative. However, usage of SMS texting has previously been shown to be widely used in older populations with arthritis [72]. This study is reported in line with SPIRIT guidelines [32] as guidelines for cohort study protocols are not fully developed [73].

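### Construct validity is assigned to confirmatory factor analysis, which repeats the structural-validity test and cannot tell a central-mechanisms factor from general distress

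*Protocol article*

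**What the plan says.** All references are to the protocol article. The Statistical analysis section names the properties that make up the primary objective: "structural validity, construct hypothesis testing, internal consistency, reliability, measurement error and criterion validity". Structural validity and construct hypothesis testing are thus two separate entries.

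The methods follow:

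- **Structural validity:** "Structural validity will be assessed using confirmatory factor analysis (CFA) and Rasch modelling".
- **Construct validity, definition:** "The construct validity of the CAP-RA questionnaire, a measure of the degree to which scores are consistent with a hypothesis".
- **Construct validity, method:** it "will be investigated using confirmatory factor analysis. Appropriate fit statistics will be calculated".
- **Criterion validity:** "Criterion validity will be a measure of the degree to which the instrument is an adequate reflection of central sensitisation". That sentence names no method.

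Outside measures appear in other places. Thresholds are to come from "receiver operating curves plotted using dichotomised outcome measures, such as the different QST measurements" (Statistical analysis). The Abstract promises validation against psychophysical indices and patient-reported measures of related traits. The Discussion says that CSI-9, painDETECT and QST will be examined as predictors in the same manner as CAP-RA. Limitations states "We attempt to address this by testing CAP-RA against QST, as a proxy for central pain mechanisms", and adds that "there is no gold standard for measuring CS which is itself a multidimensional construct".

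**The concern.** By the article's own definition, construct validity asks whether scores behave as a hypothesis about the construct predicts. The method attached to it asks whether a factor model reproduces the covariances of the modelled variables. The only variables the article describes for such a model are the questionnaire items, so the analysis would test dimensionality a second time.

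The rival explanation is concrete. The Discussion reports that the traits forming a single factor in knee osteoarthritis include catastrophising, depression, anxiety, sleep disturbance and fatigue. A factor dominated by general distress could also hold such items together. The questionnaire is meant to stratify people towards mechanism-based treatment, so what the score measures matters as much as whether its items cohere. Under the stated method, construct validity could be declared from inter-item correlation alone.

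**Working it through.** The plan states no figure on this point, so there is none to reproduce. The check has three parts.

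**1. Property against method (Statistical analysis)**

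| Property | Question asked | Method named |
|---|---|---|
| Structural validity | Do the items reflect the intended dimensionality? | CFA and Rasch |
| Construct validity | Do scores agree with a hypothesis about the construct? | CFA with fit statistics |
| Criterion validity | Do scores reflect central sensitisation? | None in that sentence |

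The second row repeats a method from the first and does not answer its own question.

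**2. Can item fit identify the factor?**

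A one-factor model implies the item covariance matrix Σ = λλ′ + Ψ. CFI and RMSEA compare Σ with the observed item covariances. No outside variable enters, so fit cannot depend on what the factor correlates with.

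An illustration: 8 items, n = 250, 400 replicates, maximum-likelihood one-factor CFA. The loadings (0.65 each) and the factor's correlations with a QST index and a distress measure are assumptions, not figures from the article.

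| Factor (assumed correlation with QST, distress) | CFI | RMSEA | Alpha | Score–QST r | Score–distress r |
|---|---|---|---|---|---|
| Central (0.60, 0.30) | 0.995 | 0.015 | 0.85 | 0.56 | 0.28 |
| Almost pure distress (0, 0.95) | 0.995 | 0.016 | 0.85 | 0.01 | 0.88 |
| Neither (0, 0) | 0.996 | 0.014 | 0.85 | 0.00 | 0.00 |

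A hand check agrees:

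- Alpha = 8 × 0.65² / (1 + 7 × 0.65²) = 3.38 / 3.9575 = 0.854.
- Expected score correlation = factor correlation × √0.854 = factor correlation × 0.924. This gives 0.60 × 0.924 = 0.55, 0.30 × 0.924 = 0.28 and 0.95 × 0.924 = 0.88.

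Fit and internal consistency are the same in all three rows. Only the last two columns differ.

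**3. Could the planned sample support a hypothesis-based test?**

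The Sample size section gives 250 recruited and 200 expected to complete. The Fisher interval is tanh(atanh r ± 1.96/√(n − 3)), and the r values are illustrative.

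- r = 0.30, n = 250: tanh(0.3095 ± 1.96/√247) = 0.18 to 0.41.
- r = 0.30, n = 200: 0.17 to 0.42.
- r = 0.50, n = 250: 0.40 to 0.59.
- r = 0.50, n = 200: 0.39 to 0.60.

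These intervals show that the remedy is feasible. They do not measure the size of the error.

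**The case against.** The strongest reply is that external testing is already planned, partly within the primary objective. Criterion validity is defined against central sensitisation, the Abstract promises comparison with psychophysical and patient-reported measures, and QST also serves for thresholds and prediction. This stands. A reader might infer that CAP-RA would never be set against a measure of central mechanisms, and the documents do not support that reading. What remains is that none of these comparisons is given as the construct-validity analysis. The article itself concedes that no gold standard exists, so the QST comparison is in substance construct hypothesis testing under another name. It also leaves discrimination unaddressed. HADS is collected, but no test of CAP-RA against distress is stated. Inflammation appears as a contributor to pain and an expected moderator, not as a discriminant comparator.

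Secondly, the construct-validity sentence does not say which variables enter the CFA. A model with external measures as further factors could test convergent and discriminant validity. That is true, but no such model is described, and only fit statistics are named.

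Thirdly, exact hypotheses, expected sizes and a pass rule are usually left to an analysis plan. This also stands, and their absence is not the point here. The point is that the article names a method, and the method does not match the property.

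Finally, the simulation shows a general feature of CFA and is not a result for this instrument. A reader should not infer that the CAP-RA items would fit a distress factor equally well. The knee trait also includes neuropathic pain and pain distribution, and the article gives no item data.

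**Conclusion.** The concern holds in a limited form. Two properties that the article separates receive the same test, and for construct validity that test cannot show what the factor represents. In the illustration, a central factor and a distress factor both gave CFI 0.995, while their correlations with the QST index were 0.56 and 0.01.

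The conclusion rests on reading the CFA as a model of the questionnaire items. It does not depend on the assumed loadings, because fit to the items never involves outside variables. Since external comparisons are planned elsewhere, and no change to recruitment, measurement or sample size is needed, this is a should-fix matter.

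**What to change.** Restrict CFA and Rasch to structural validity. State that construct validity will be assessed on baseline data by directional hypotheses fixed before analysis:

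- **Convergent:** higher CAP-RA goes with higher CSI-9, painDETECT and WPI/SSS, lower PPT, greater TS (series minus single rating) and lower CPM (post minus pre, as the article defines it).
- **Discriminant, inflammation:** weaker association with ESR/CRP, swollen joint count and ultrasound scores than with the central measures.
- **Discriminant, distress:** the association with QST persists after adjustment for HADS. Report it with and without adjustment, since depression and anxiety are among the traits in the construct and some attenuation is to be expected.

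Expected sizes and the share of hypotheses that must hold can be left to the analysis plan. The QST comparison now described as criterion validity could be cross-referenced here, given the stated lack of a gold standard.

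The cost is a short hypothesis table and a few extra analyses of data already being collected. The real downside for the sponsor is that the instrument can then fail the test.

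### Criterion validity for central sensitisation cannot be established when the protocol says no gold standard exists, and any ROC-derived CAP-RA cut-off needs optimism correction and a provisional label

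*Protocol article*

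**What the plan says.** The Statistical analysis section of the protocol article states that the properties examined under the primary objective will include "structural validity, construct hypothesis testing, internal consistency, reliability, measurement error and criterion validity". It describes the last of these in one sentence: "Criterion validity will be a measure of the degree to which the instrument is an adequate reflection of central sensitisation". That sentence names no criterion measure. The same section says construct validity will be investigated by confirmatory factor analysis and mentions no other method for it.

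The Limitations section then says of CS that "there is no gold standard for measuring CS which is itself a multidimensional construct". It describes the role of QST as follows: "We attempt to address this by testing CAP-RA against QST, as a proxy for central pain mechanisms". It adds: "Each QST modality might have different measurement properties and indicate different aspects of CS".

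Under Clinical assessment, "Quantitative sensory testing will be conducted using Pressure Pain detection Threshold (PPT), Temporal Summation (TS) and Conditioned Pain Modulation (CPM) tests". PPT is taken at three sites, so with TS and CPM there are five continuous QST indices.

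For thresholds, the Statistical analysis section says that CAP-RA cut-points marking high levels of central pain mechanisms "will be derived through receiver operating curves plotted using dichotomised outcome measures, such as the different QST measurements". The Objectives include scoring recommendations for stratifying patients both in trials and in practice.

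**The concern.** There are two separate issues.

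The first is the label. Criterion validity, in its usual sense, is agreement with an accepted reference standard. The article says that none exists for CS and that its comparator is a proxy. Comparing a questionnaire with a proxy tests a hypothesis about the construct, which is construct validity. The article attaches that term only to factor analysis, which examines how the items hang together and not how the score relates to QST. The QST comparison is therefore left without a correct label, and a good result could be reported as criterion validity that the design cannot show.

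The second is the threshold. A cut-off chosen to maximise separation in one sample looks better in that sample than it will elsewhere, and it moves from sample to sample. Using several proxies that may index different things gives one candidate cut-off per proxy. The cut-offs are meant to stratify patients, so a shift of several points would put many people in a different group.

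**Working it through.** **Label.** No arithmetic applies. Set side by side:

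- Statistical analysis: criterion validity is among the primary-objective properties and is defined by reference to CS.
- Limitations: CS has no gold standard, and QST is a proxy for it.
- Statistical analysis: construct validity is to be investigated by confirmatory factor analysis.
- Abstract, Methods/design: QST modalities are the indices of CS. Abstract, Discussion: the questionnaire will be validated against psychophysical indices and related patient-reported measures.

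The first two statements cannot both stand. The last two show that an external comparison is planned, and the article gives it no place other than criterion validity.

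**Threshold.** The article gives no figure for ROC, cut-off or AUC precision, so there is none to reproduce. Its sample-size section covers Rasch calibration, a regression and an ICC, with 250 recruited and 200 expected to complete.

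Input from the article: n = 250 at baseline. Assumptions not in the documents:

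- CAP-RA is scored 0–16, with mean 8 and SD 3.5.
- The score and each QST index are bivariate normal, with correlation r.
- The worst third of each index is called high.
- The cut-off maximises the Youden index, J = sensitivity + specificity − 1.

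In repeated simulated samples, apparent J is the value in the sample that chose the cut-off. True J is the value of that same cut-off in a very large population.

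| Assumed r | 95% range of cut-off (points) | Apparent J | True J | Median spread over five indices (points) |
|---|---|---|---|---|
| 0.2 | 5–12 | about 0.16 | about 0.11 | 3–4 |
| 0.3 | about 6–11 | about 0.23 | about 0.18 | 2–3 |
| 0.5 | 7–11 | about 0.36 | about 0.33 | 2 |

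A separate run at three decimals gave 0.168 against 0.117 at r = 0.2, and 0.226 against 0.182 at r = 0.3. Relative optimism is then:

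- r = 0.2: (0.168 − 0.117) / 0.168 = 0.051 / 0.168 = 30%
- r = 0.3: (0.226 − 0.182) / 0.226 = 0.044 / 0.226 = 19%
- r = 0.5: (0.36 − 0.33) / 0.36 = 0.03 / 0.36 = 8%

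The spread over indices arises although all five were given the same true relation to CAP-RA. Residual correlation between indices narrows it: at r = 0.3 the median falls from 3 points to 2 when that correlation rises from 0.3 to 0.6. Truly different relations to CAP-RA would widen it.

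**AUC precision.** The Hanley–McNeil variance is [A(1−A) + (n₁−1)(Q₁−A²) + (n₀−1)(Q₂−A²)] / (n₁n₀), with Q₁ = A/(2−A) and Q₂ = 2A²/(1+A). For A = 0.60 and 125 per group, Q₁ = 0.4286 and Q₂ = 0.45. The variance is (0.24 + 124 × 0.0686 + 124 × 0.09) / 15,625 = 0.00127, so the 95% half-width is 1.96 × 0.0357 = 0.070. With a 25% split it is 0.083.

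**Information lost.** Splitting a normal variable at its median keeps about 2/π = 64% of its information. This is why the association itself is better reported with QST continuous.

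**The case against.** The strongest reply has four parts.

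*The limitation is disclosed.* The article says openly that QST is a proxy and that modalities differ. That is true and to its credit. But the disclosure is what makes the criterion-validity label untenable, so it does not settle the label.

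*The article does not say what a critic might infer.* A reader might infer that criterion validity itself rests on dichotomised QST. The text does not say so: the criterion-validity sentence names no measure, and dichotomising appears only for thresholds, which serve a secondary objective. A reader might also infer that five competing cut-offs will be issued, or that accuracy will be reported uncorrected. Neither is stated. QST is given as an example of the reference measures, and no cut-off rule is named. These objections stand.

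*Detail belongs elsewhere.* The governing reference, the QST cut-points, how the curves are reconciled and internal validation may all be in the full protocol or analysis plan. Their absence from an article is no finding. Examining modalities separately is also defensible if they capture different aspects of CS, and a conventional ROC curve needs a binary reference whichever anchor is used. This stands too.

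*The effect may be small.* J is flat near its maximum, so a misplaced cut-off costs little. The chosen cut-off averages 0.116 against a best attainable 0.130 at r = 0.2, and 0.326 against 0.341 at r = 0.5, a loss of about 0.015. Optimism is only 0.03 to 0.05 in absolute terms. These figures are right. They limit the harm to overall accuracy, but not the movement of individual patients across a cut-off that shifts by several points.

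**Conclusion.** The labelling point holds on the text alone and needs no assumption: by its own account of CS and QST, the study can test construct validity against a proxy but cannot establish criterion validity.

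The threshold point holds conditionally. It would go too far to say that the cut-offs will be unstable, conflicting and optimistic, because that depends on the CAP-RA to QST correlation, the QST split and the cut-off rule, none of which the documents give. Under the assumptions stated, a weak correlation (0.2) gives a cut-off uncertain over about 5 to 12 points of a 16-point scale and apparent accuracy overstated by roughly 30%. At a correlation of 0.5 the range is 7 to 11 and the overstatement about 8%. The problem shrinks but does not vanish.

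Both points affect what the study may claim, not whether it can be run. They are worth correcting before analysis.

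**What to change.** 1. In the Statistical analysis section, replace criterion validity with construct validity (hypothesis testing). State that this is assessed by associations between CAP-RA and the QST indices kept continuous, and keep factor analysis under structural validity.
2. For any ROC-derived threshold, repeat the whole cut-off selection in bootstrap samples. Report a confidence interval for the cut-off, with optimism-corrected sensitivity, specificity and AUC.
3. Describe any such cut-off as provisional until tested in another cohort, including where it feeds the stratification recommendations.

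Naming one primary anchor for the threshold in advance is advisable, but it is a design choice and may already be in the full plan.

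The cost is a change of wording and a bootstrap, with no new data. The downside is slightly less favourable accuracy figures and a weaker validity label.
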